**Fig. 1 Fig1:**
[figure not shown]
Study flow diagram

### Retention

Participants are reimbursed $200 (NZD) in recognition of travel and time. Reminders for weekly study diary completion are sent to non-responders once daily for five days, after which the diary window is closed.

### Permitted and prohibited concomitant treatment

No other eczema treatments or moisturisers will be permitted during the trial. Participants can continue with all other prescribed medication. Concomitant medication usage will be collected in the weekly participant diaries, which ask asked if participants have used any medications other than their study treatment in the last week, prompts them to leave details and MRINZ investigators will contact the participant directly to complete concomitant medication forms based on C-DASH standards. It is recognised that minor exacerbations of eczema are expected, therefore the usage of topical corticosteroids habitually used by the participant, for a duration of less than or equal to seven days, is permitted without requiring withdrawal from the study. The requirement for escalated treatment will be recorded and compared between treatment groups.

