### Participant timeline

Upon presentation to the pharmacy, consent, demographic data, eligibility, and baseline data are collected, followed by a clinical photograph of a representative eczema lesion, chosen by the participant. The participant is randomised, and the appropriate treatment is dispensed by the study pharmacist along with the aqueous cream. Over the six-week interventional period, participants complete a weekly digital diary to report POEM, treatment adherence, adverse events, and use of concomitant medications (Table 2). Participants return to the pharmacy for a second face to face visit at week six including a second clinical photograph of the representative lesion. A final electronic follow up survey is completed at week eight to collect any adverse events following the cessation of study treatment. The study flow is depicted in Fig. 1*.*

**Table 2 Tab2:** Summary of study procedures

	Visit 1	Treatment Period					Visit 2	Follow Up Survey
Day	**0**	**7**	**14**	**21**	**28**	**35**	**42 (+ 5)**	**14 days post Visit 2 (+ 5)**
Eligibility screen	X							
Informed consent	X							
Demographic data collection	X							
POEM	X	X	X	X	X	X	X	
PO-SCORAD	X						X	
SCORAD (Part B)	X						X	
DLQI	X						X	
Eczema photo	X						X	
Randomisation	X							
Dispense medication	X							
Electronic study diary		X	X	X	X	X		
Treatment compliance		X	X	X	X	X	X	
Adverse event collection		X	X	X	X	X	X	X
TSQM Version II							X	
Acceptability NRS							X

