### Data capture

All study related data, including informed consent, will be captured using e-source via REDCap-based case report forms [55]. REDCap is a secure, United States Health Insurance Portability and Accountability Act 1996 (HIPAA) compliant web-based application designed to support data capture for research studies. CDASH-compliant structures are used to collect standard data types required for this study. Data is entered into tablet devices at pharmacy sites. Online study diaries and questionnaires completed by study participants are accessed via a link unique to each participant for each time point. The usage of electronic data capture allows for data validation using data entry ranges, required data fields, and logic checks. Study data is stored on secure password protected servers and only accessible by trial staff and independent study auditors, investigators will retain access to the final trial dataset.

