### Outcome measures

#### Primary

Primary outcome is severity assessed by subjective symptoms over six weeks, measured by change in POEM scores, adjusted for baseline. The POEM tool assesses severity of eczema by capturing self-reported frequency of symptoms over the previous seven days [54]. Scores can range from 0 to 28, with higher scores indicating a higher severity of disease. The following bandings have been established: Clear or almost clear (0–2); Mild eczema (3–7); Moderate eczema (8–16); Severe eczema (17–24); Very severe eczema (25–28).

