#### Secondary

Secondary outcome measures include participants who had a four or greater reduction in POEM score (termed ‘responders’ [56]); the difference in POEM scores analysed per protocol; the difference in POEM scores; the difference in Patient Oriented SCORing Atopic Dermatitis (PO-SCORAD) [57]; the difference in pharmacist-assessed SCORing Atopic Dermatitis (SCORAD) score (part B only) [58]; withdrawals due to the exacerbation of eczema; the proportion of treatment escalation between groups; the difference in Dermatology Life Quality Index (DLQI) [59, 60]; participant acceptance of the treatment measured by Treatment Satisfaction Questionnaire for Medication (TSQM) Version II [61]; Numerical Rating Scale (NRS) of the acceptability of the treatment; the proportion of cutaneous and systemic events between the treatment groups; the difference in SCORAD scores between blinded pharmacist and blinded dermatologist; and the difference in SCORAD scores between pharmacists. For full schedule of interventions and assessments see Table 2*.*

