#### Statistical analysis

Primary outcome analysis, and analysis of secondary POEM, PO-SCORAD, and DLQI outcomes will be by ANCOVA with baseline POEM score as a continuous covariate, and randomised treatment as a categorical variable of interest. Analysis of proportions will be by estimation of relative risk and associated confidence intervals. Participant acceptability will be assessed by t-test, or if normality assumptions are strongly violated by Mann–Whitney test with Hodges-Lehmann estimator of location. Comparison of SCORAD scores between pharmacists and between pharmacist and dermatologist will be by linear mixed model with participant treated as a random effect.

Analysis will be separated by intention-to-treat (ITT) and per protocol set (PPS), with ITT as the primary analysis. ITT population is all participants randomised. PPS is all participants with at least 80% completed data, including primary outcome with no significant protocol deviations determined to influence POEM score. For inclusion in PPS, participants should adhere to treatment instructions, measured by > 80% daily adherence. Missing outcome data will not be imputed. No interim analyses are planned and SAS will be used for analysis.

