#### Power calculation

The sample size calculation is based on a minimal clinically important difference (MCID) of 3.4 [62] and pooled standard deviation (SD) of 6.0 for the change in POEM score [52]. With 80% power, and 5% two-sided alpha, each treatment group would require 50 participants. Allowing for 15% withdrawal and loss to follow up, 118 participants total are required for this study.

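### The seven-day steroid rule is worded as withdrawal from the study, so outcomes may go uncollected for participants whose eczema does badly; stopping the cream should be separated from leaving follow-up

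*Protocol article*

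**What the plan says.** Under Permitted and prohibited concomitant treatment, the article expects minor flares and says that use of a participant's usual topical corticosteroid "for a duration of less than or equal to seven days, is permitted without requiring withdrawal from the study". The same section says escalated treatment will be recorded and compared between arms.

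Four other places bear on this:

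- **Secondary outcomes:** the list includes "withdrawals due to the exacerbation of eczema".
- **Statistical analysis:** "ITT population is all participants randomised", and "Missing outcome data will not be imputed".
- **Power calculation:** "Allowing for 15% withdrawal and loss to follow up, 118 participants total are required for this study".
- **Primary outcome:** "Primary outcome is severity assessed by subjective symptoms over six weeks, measured by change in POEM scores, adjusted for baseline".

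On collection, Participant timeline says that "participants complete a weekly digital diary to report POEM, treatment adherence, adverse events, and use of concomitant medications", and Data capture says that "Online study diaries and questionnaires completed by study participants are accessed via a link unique to each participant for each time point". Table 2 schedules the electronic diary for days 7 to 35. The day-42 POEM belongs to Visit 2, which Table 1 allows by telephone if required by COVID restrictions or an unforeseen inability to attend. A survey two weeks after Visit 2 collects adverse events.

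**The concern.** The steroid sentence has a purpose only if use beyond seven days does require withdrawal, and what it names is the study, not the study cream. The article describes no status in which a participant stops the cream but stays in follow-up.

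An intention-to-treat comparison needs outcomes to be collected after rescue treatment and after the cream is stopped. Here the event that would end participation is itself a sign of how the eczema is doing. The rate may differ by arm: fewer flares on active cream if it works, more if it irritates. Under Randomisation and masking, participants are assumed to be unblinded by smell, which may also affect how readily they turn to their steroid.

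This is a matter of collection and is separate from the no-imputation statement. A model for missing scores has to rest on assumptions that collected scores would make unnecessary. At stake for these participants are the later POEM scores including day 42, the day-42 DLQI, and possibly later adverse events.

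**Working it through.** **1. The plan's own sample size.** Inputs from Power calculation: difference 3.4, SD 6.0, two-sided alpha 5%, power 80%, 15% loss.

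- A two-sample t-test with effect size 3.4/6.0 = 0.567 needs 49.86, so 50 per arm (power 80.1%).
- Total: 100/(1 − 0.15) = 117.6, so 118, or 59 per arm.

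Both stated figures reproduce. The calculation allows for 118 − 100 = 18 participants without a primary outcome, and withdrawals are among them.

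**2. Shift in the contrast.** The primary outcome is taken here as the day-42 change, because the ANCOVA has only baseline and treatment as terms. Let w be the share of an arm that leaves under the rule, and D the number of points by which the leavers' day-42 change would have been worse than that of those who stay. The mean of those who stay then exceeds the full-arm mean by w × D, and the contrast shifts by D × (w for vehicle − w for active).

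The article gives neither w nor D. Assume 6 of 59 vehicle and 2 of 59 active participants leave, with D = 6 (range 3 to 8):

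- Vehicle: 6/59 × 6 = 0.61
- Active: 2/59 × 6 = 0.20
- Shift: 0.61 − 0.20 = 0.41
- At D = 3: 4/59 × 3 = 0.20
- At D = 8: 4/59 × 8 = 0.54

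Against a true difference of 3.4, that is about 6% to 16% (0.20/3.4 and 0.54/3.4).

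**3. Other assumed loss patterns.** Observed difference = 3.4 − D × (w for vehicle − w for active). Power is by normal approximation with 59 × (1 − w) followed per arm.

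| Loss, active / vehicle | D = 3.4 | D = 6 | D = 8 |
|---|---|---|---|
| 15% / 15% | 3.40 (81%) | 3.40 (81%) | 3.40 (81%) |
| 5% / 15% | 3.06 (75%) | 2.80 (67%) | 2.60 (61%) |
| 7.5% / 22.5% | 2.89 (67%) | 2.50 (55%) | 2.20 (45%) |

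The last row is a stress case: it assigns the whole 15% allowance to this one cause, with a threefold imbalance.

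**4. Direction.** If leavers would have done worse and more of them are on vehicle, the observed contrast shrinks. If more are on active, it grows. If a longer steroid course would have left the leavers with better day-42 scores than those who stayed, D is negative and each direction reverses.

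**5. Precision.** Keeping the 8 assumed leavers gives 100 + 8 = 108 participants, or 54 per arm, with power about 83% against 80.1%. Following all 59 per arm would give 86.3%. That is an upper bound, because it assumes no other loss and the same effect and SD after longer steroid use.

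**The case against.** The strongest reply is that the rule is inferred. The steroid sentence says what does not require withdrawal; it does not say that longer use ends participation, and nothing says that collection stops at withdrawal. The article condenses a full protocol that may set out follow-up after withdrawal, and the flow diagram is not shown. The 15% allowance is ordinary wording and also covers withdrawn consent. All of this stands, and it limits the point to what the sentence implies. It does not remove the point: a site that reads the sentence literally would stop collection, so the wording needs correcting even if follow-up is meant to continue.

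Three stronger readings are tempting and are not supported:

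- **That the all-randomised set as a whole stops being followed.** Only participants over the steroid limit are affected, and their earlier weekly POEM scores remain.
- **That treatment escalation is lost.** The escalation that triggers withdrawal is recorded and compared, and exacerbation withdrawals are themselves an outcome. Only escalation after that point could be missed. Loss of later adverse events is possible but not shown, since nothing excludes these participants from the week-eight survey and ad-hoc contact is allowed.
- **That POEM needs only an electronic link.** That holds for the weekly diaries. The day-42 score belongs to Visit 2, although a telephone route exists and POEM is self-reported.

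It is also fair to say that the loss rates and point differences are assumptions, and that the central shift of about 0.4 points is modest.

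**Conclusion.** The point holds in a limited form. Read as written, the article implies that participants over the steroid limit leave the study. Combined with an all-randomised analysis without imputation, that would lose outcomes for a reason related to response. The inflation to 118 replaces numbers but cannot remove a bias of this kind.

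The size and direction are unknown. On the assumed 6/59 and 2/59 losses with a 3 to 8 point difference, the contrast moves by about 0.2 to 0.54 points against 3.4. Larger imbalances would do more harm. Equal loss with equal deficit gives no bias, only lost precision. The change is worth making because it is cheap, and confidence is medium because both the withdrawal and the end of collection are implied, not stated.

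**What to change.** - State that passing the steroid limit, or stopping the cream, is not withdrawal from follow-up. Unless consent is withdrawn, continue the weekly POEM link, the day-42 POEM (by visit, telephone or link) and the week-eight survey.
- Include these scores in the ITT analysis, and say that the primary estimate follows a treatment-policy reading, that is, scores count regardless of rescue or stopping.
- Reword the secondary outcome on exacerbation withdrawals as discontinuation of study treatment due to exacerbation. Otherwise, once withdrawal no longer covers these participants, that outcome would be emptied.
- If the full protocol already provides for such follow-up, the steroid sentence need only be brought into line with it.

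The seven-day limit, and any rule on when the cream is stopped, are left to the sponsor.

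**Cost:** a few sentences by amendment and keeping existing REDCap links open. There is a little more follow-up contact, because positive medication or adverse-event answers lead to a call from the central investigators. The downside is that scores obtained after rescue enter the primary estimate, which then describes the effect of assignment to the cream with rescue as used.

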### Data capture

All study related data, including informed consent, will be captured using e-source via REDCap-based case report forms [55]. REDCap is a secure, United States Health Insurance Portability and Accountability Act 1996 (HIPAA) compliant web-based application designed to support data capture for research studies. CDASH-compliant structures are used to collect standard data types required for this study. Data is entered into tablet devices at pharmacy sites. Online study diaries and questionnaires completed by study participants are accessed via a link unique to each participant for each time point. The usage of electronic data capture allows for data validation using data entry ranges, required data fields, and logic checks. Study data is stored on secure password protected servers and only accessible by trial staff and independent study auditors, investigators will retain access to the final trial dataset.

### Monitoring

A study monitoring plan, independent from the Sponsor, is in place to ensure all study conduct complies with International Council for Harmonisation of Technical Requirements for Registration of Pharmaceuticals for Human Use, Good Clinical Practice and New Zealand ethical guidelines. All substantial protocol deviations and violations will be reported to the New Zealand ethics committee as per approval requirements.

### Outcome measures

#### Primary

Primary outcome is severity assessed by subjective symptoms over six weeks, measured by change in POEM scores, adjusted for baseline. The POEM tool assesses severity of eczema by capturing self-reported frequency of symptoms over the previous seven days [54]. Scores can range from 0 to 28, with higher scores indicating a higher severity of disease. The following bandings have been established: Clear or almost clear (0–2); Mild eczema (3–7); Moderate eczema (8–16); Severe eczema (17–24); Very severe eczema (25–28).

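### The primary POEM outcome does not name its time point; read as Day 42, its ANCOVA without imputation discards the weekly POEMs of participants who miss that visit

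*Protocol article*

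**What the plan says.** All references are to the protocol article.

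- **Outcome measures, Primary:** "Primary outcome is severity assessed by subjective symptoms over six weeks, measured by change in POEM scores, adjusted for baseline". No visit is named.
- **Participant timeline:** "participants complete a weekly digital diary to report POEM, treatment adherence, adverse events, and use of concomitant medications". Table 2 schedules POEM on Day 0, Days 7 to 35 by diary, and Day 42 at Visit 2, which makes six post-baseline scores.
- **Outcome measures, Secondary:** the list contains "the difference in POEM scores analysed per protocol; the difference in POEM scores". The second item has no analysis set, visit or summary attached.
- **Statistical analysis:** one model covers both kinds of POEM outcome, since "analysis of secondary POEM, PO-SCORAD, and DLQI outcomes will be by ANCOVA with baseline POEM score as a continuous covariate" and the primary is named in the same sentence. Treatment arm is the only other term. The primary set is everyone randomised, and missing outcomes are not imputed.
- **Randomisation and masking:** allocation is stratified by site. Trial setting and recruitment expects 10 to 15 pharmacies.
- **Power calculation:** an "minimal clinically important difference (MCID) of 3.4", a "pooled standard deviation (SD) of 6.0 for the change in POEM score", and "With 80% power, and 5% two-sided alpha, each treatment group would require 50 participants", raised to 118 in total for 15% loss. No time point is given here either.

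**The concern.** A change over six weeks, with six scores in those weeks, can be read as the change to the last score or as a summary across all of them. The separate secondary POEM difference makes the reader ask what distinguishes it from the primary. Under the stated model it may be nothing at all.

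The larger matter appears once the wording is settled as Day 42. A single-visit ANCOVA uses only participants with a Day 42 score. Someone who completes five diaries and then misses Visit 2 counts in the intention-to-treat set by name but adds nothing to the primary estimate. If those who leave differ between arms in how their eczema was going, the primary estimate is biased, although the trial holds the scores that could correct much of that.

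**Working it through.** **1. The plan's sample size.** Inputs from Power calculation: difference 3.4, SD 6.0, two-sided alpha 5%, power 80%.

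- Normal approximation: n = 2 × (1.960 + 0.842)² × 6.0² / 3.4² = 2 × 7.85 × 36 / 11.56 = 48.9, so 49 per arm.
- t-test: power 79.3% at 49 and 80.1% at 50, so 50 per arm.
- Inflation: 100 / (1 − 0.15) = 117.6, so 118.

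Both stated figures reproduce.

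**2. Power on the Day 42 reading.** Assume equal variances and a correlation r between baseline and Day 42 (not given in the article). From 36 = 2σ²(1 − r), σ² = 18/(1 − r). The ANCOVA residual variance is σ²(1 − r²) = 18(1 + r).

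| r | residual variance | residual SD | power, 50 completers per arm |
|---|---|---|---|
| 0.3 | 23.4 | 4.84 | 94% |
| 0.5 | 27.0 | 5.20 | 90% |
| 0.7 | 30.6 | 5.53 | 86% |

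Power exceeds the stated 80% throughout.

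**3. Primary against secondary POEM difference.** Write Y₀ and Y₆ for baseline and Day 42 POEM, and T for treatment. The model Y₆ − Y₀ = a + τT + bY₀ + e is the same as Y₆ = a + τT + (b + 1)Y₀ + e. The treatment effect τ, its standard error and its p-value are identical. A numerical check gave an estimate of −3.254 and p = 0.00126 both ways. If both outcomes mean Day 42 in the same analysis set, the secondary repeats the primary.

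**4. Who drops out of the primary estimate.** The plan allows for 118 − 100 = 18 participants without the final outcome. With no imputation and one visit in the model, all of their diary POEMs are unused.

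**5. What that can cost.** In simulation with a true Day 42 difference of 3.4, assumed between-visit correlations and 15% dropout depending on earlier scores in one arm, complete-case ANCOVA was biased by about 0.15 to 0.2 points. That is 0.15/3.4 = 4% to 0.2/3.4 = 6% of the difference. A repeated-measures model on all weekly scores had almost no bias and slightly better precision. The bias depends on how strongly dropout follows earlier scores. It all but disappears when that link is the same in both arms or absent.

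**6. Site.** Randomisation is stratified by site, but the model contains only baseline POEM and treatment. With 10 to 15 sites there are about 118/15 = 8 to 118/10 = 12 participants per site, enough to carry a site term. Leaving out a stratification factor usually makes the standard error too large rather than too small, so this is lost precision and not a false-positive problem.

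**The case against.** The best reply is that the article already points to one reading. An ANCOVA without a time term takes one value per participant. Where there are several values per participant, in the SCORAD rater comparisons, the same section names a mixed model. PO-SCORAD and DLQI share the ANCOVA sentence and are collected only at Day 0 and Day 42. Treatment ends at week six, and no section mentions an average or an area under the curve. This stands: Day 42 is the natural reading, and naming it is mostly a clarification.

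A reader might infer more: that the confirmatory contrast is open, that the trial may be powered for the wrong one, and that alpha is inflated. Calculations can be made to look that way. With r from 0.3 to 0.7, a six-week average has power of about 70% to 92% if the effect builds linearly to 3.4 (average difference 1.98), and at least 99% if it is immediate. Choosing after the fact between Day 42 and the average gives 8% to 9% false positives, and choosing among six weekly contrasts gives about 22% to 25%. The documents do not support the inference. They offer neither the average nor the early weeks as a candidate primary, and the correlations and effect patterns are assumptions.

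It can also be said that a single-visit ANCOVA is valid and standard, that a repeated-measures model is a preference, and that the full protocol or analysis plan may give the details. The first is true when outcomes are complete or missingness is unrelated to outcome. But this plan expects 15% loss, rules out imputation and has weekly scores in hand, so the better method is available at almost no cost. The time point of the primary outcome belongs where that outcome is stated.

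**Conclusion.** The concern holds in a limited form. The primary outcome lacks a named time point, and the secondary POEM difference is either a duplicate or undefined. Read as Day 42, the sample size is adequate, and no power or type I error is shown.

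The substantive point is efficiency and robustness: about 18 of 118 participants may be left out of the primary estimate despite having weekly POEMs, and site is missing from the model. The likely size is modest, about 0.15 to 0.2 points on 3.4 under assumed correlations and one-arm dropout linked to earlier scores. The bias could shrink or enlarge the estimated effect, depending on which arm loses its worse-scoring participants. The repeated-measures model removes it only so far as the recorded scores explain the dropout, and participants who leave before any diary still contribute nothing.

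**What to change.** 1. In Outcome measures, Primary, state that the primary outcome is the between-arm difference in POEM at Day 42 (Visit 2), adjusted for baseline POEM, in all randomised participants. In Power calculation, give the time point to which the SD of 6.0 refers.
2. In Statistical analysis, estimate it from one repeated-measures mixed model on all Day 7 to Day 42 POEMs, with treatment by week, baseline POEM by week, site, and an unstructured covariance. Day 42 is the only confirmatory contrast. The rule against imputation can stay, because the model imputes nothing.
3. In Outcome measures, Secondary, redefine the POEM difference as the weekly contrasts and the six-week average from the same model, as supportive results.

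The cost is a few sentences and a standard SAS model, with no new data and no change to the sample size. Trial status describes enrolment as continuing, so the change can precede analysis. The downside is that a covariance structure must be prespecified, and the precision gain is small when dropout is unrelated to outcome.
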